## Abstract

**Background:**

Adherence to therapies is a primary determinant of treatment success, yet the World Health Organisation estimate that only 50% of patients who suffer from chronic diseases adhere to treatment recommendations. In a previous project, we found that 30% of stroke patients reported sub-optimal medication adherence, and this was associated with younger age, greater cognitive impairment, lower perceptions of medication benefits and higher specific concerns about medication. We now wish to pilot a brief intervention aimed at (a) helping patients establish a better medication-taking routine, and (b) eliciting and modifying any erroneous beliefs regarding their medication and their stroke.

**Methods/Design:**

Thirty patients will be allocated to a brief intervention (2 sessions) and 30 to treatment as usual. The primary outcome will be adherence measured over 3 months using Medication Event Monitoring System (MEMS) pill containers which electronically record openings. Secondary outcomes will include self reported adherence and blood pressure.

**Discussion:**

This study shall also assess uptake/attrition, feasibility, ease of understanding and acceptability of this complex intervention.

**Trial Registration:**

Current Controlled Trials ISRCTN38274953

## Background

Adherence to therapies is a primary determinant of treatment success. Poor adherence attenuates optimum clinical benefits and therefore reduces the overall effectiveness of health systems, yet it is estimated that in developed countries, only 50% of patients who suffer from chronic diseases adhere to treatment recommendations [1]. In the treatment of hypertension, it has been estimated that only 30-50% of patients regularly take their antihypertensive drugs as prescribed, and that non-adherence may cause half of antihypertensive drug "failures" [2]. A recent illustrative example from the field of cardiovascular disease is provided by the Duke Databank for Cardiovascular Disease for the years 1995 to 2002, which assessed the annual prevalence and consistency of self-reported use of aspirin, β-blockers, lipid-lowering agents, and combinations of the 3 drugs in patients with coronary artery disease. Rates of consistent self-reported medication use were sobering: aspirin (71%), β-blocker (46%), lipid-lowering agent (44%), aspirin and β-blocker (36%), and 21% for all 3 medications. Overall, consistent use was associated with lower adjusted mortality, although in this study the authors were unable to differentiate patient non-adherence from physician non-prescription [3]. In a further study of drug adherence and mortality in 31,455 survivors of myocardial infarction who were taking statins and β-blockers, patients were divided into 3 adherence categories: high, intermediate and low. After 1 year, compared with the high-adherence group, low adherers to statin therapy had a 25% increased risk of mortality [4]. Thus, polypharmacy is the norm, self-reported adherence is often suboptimal, and this is associated with elevated mortality risk [5].

The most recent Cochrane review of interventions to improve medication adherence concluded that, "Current methods of improving adherence for chronic health problems are mostly complex and not very effective, so that the full benefits of treatment cannot be realized. High priority should be given to fundamental and applied research concerning innovations to assist patients to follow medication prescriptions for long-term medical disorders" [6]. Our aim is to improve medication adherence in the secondary prevention of stroke. Stroke is the third most common cause of death in the UK, and is the most common cause of severe physical disability amongst adults. The National Audit Office recently estimated that the annual cost of caring for people with stroke is £7 billion per year in the UK alone [7]. The risk of a recurrent stroke is 30-43% within 5 years, and it is estimated that, currently, 11,626 strokes occur annually in the Scottish population [8]. Large randomised controlled trials and meta-analyses have identified several drugs which significantly reduce the risk of future vascular events after stroke. The Scottish Intercollegiate Guidelines Network (SIGN) guidelines for secondary prevention after stroke now recommend antiplatelet therapy and reduction of both blood pressure and cholesterol level [9]. The estimated efficacy of these drugs in helping prevent a further stroke in Scotland is outlined in Table 1.

**Table 1 T1:** Estimated impact of pharmaceutical interventions to prevent recurrent strokes in Scotland

Intervention	Number of Strokes avoided	% of all strokes in Scotland
Aspirin	926	(8%)

Statins to reduce cholesterol	854	(7%)

Drugs to reduce blood pressure	751	(6%)

Dipyridamole added to aspirin	432	(4%)

Anticoagulants	376	(3%)

Taken from Health in Scotland 2007, Annual Report of the Chief Medical Officer, based on Table 18.4 in Warlow et al. [8]. The numbers in the table are derived from applying estimates from randomised trials and meta-analyses of the reduction in stroke risk achieved by adding each intervention sequentially to the previous one(s), assuming that these interventions are fully adhered to by all eligible patients with ischaemic stroke or transient ischaemic attack (TIA) in Scotland. Untreated recurrent stroke risks are derived from UK population-based stroke registry data.

A major risk factor for recurring vascular events or death is therefore non-adherence to medication, but only limited data are available on patient adherence to medication intended to prevent recurrent stroke. However, there is no reason to believe that stroke patients should demonstrate better adherence than in other chronic conditions. In fact, the reverse is more plausible, given that stroke often causes memory impairment, which is known to cause adherence problems. In a study of over 3,000 patients in Germany, Hamann et al. [10] reported that 84% were still taking aspirin at one-year post stroke, 77% oral anticoagulants, but only 61% who were prescribed clopidogrel at discharge were still taking it one year later. Sappok et al. [11] also reported from a follow-up study one year after stroke and found that only 70% of patients were still taking cholesterol-reducing treatment. Data from the Netherlands revealed that by 1 year after ischaemic stroke, 22% of patients who had been taking oral anticoagulation had stopped, half of whom did so "for non-medical reasons" such as perceived adverse effects, patient request etc. [12]. Thus, the available data on stroke patients suggest that adherence is often sub-optimal, and that many patients are consequently at a significantly increased risk of a further stroke and/or cardiovascular event.

### Fractionating Adherence

Adherence is the end result of a complex set of perceptions, attitudes, cognitive abilities, intentions and behaviours. It has proved useful to distinguish between deliberate non-adherence (intentional) and non-deliberate non-adherence (non-intentional) [1]. The aim of this pilot project is to improve intentional adherence by addressing beliefs that act as a barrier to adherence and to reduce non-intentional non-adherence by developing plans to help reduce forgetting.

#### Intentional non-adherence

Our theoretical framework is based around Leventhal's self-regulation theory [13]. This theory posits that patients have a common-sense model of their illness in terms of beliefs regarding how long a condition will last, whether it is acute or chronic, what sort of treatments will help, etc. Superimposed upon this framework of illness beliefs are beliefs about treatment, particularly the perceived necessity of medication versus concerns about possible harmful effects of medication [14]. Our recently completed study [15] on determinants of adherence in stroke patients supported self-regulation theory: it identified that stroke patients' concerns about their medication (e.g. dependence, toxicity, too many tablets) were key determinants of poor adherence. We therefore aim to elicit and attempt to modify erroneous beliefs about medication and stroke in this pilot randomised trial of a brief intervention.

#### Non-intentional non-adherence

Many patients forget to take their medication as directed. Our previous study on adherence in stroke patients established that cognitive impairment (as measured by the Mini Mental State Examination (MMSE)) was significantly associated with poor adherence [15]. An impressive body of evidence has accumulated showing that brief and easy-to-complete implementation intentions interventions are effective at reducing forgetting and in improving medication adherence [16]. These involve patients writing down **exactly when and where **they will take their medication, using the format of an if-then plan ("If it is time X in place Y and I am doing Z, then I will take my pill dose"). The evidence clearly indicates that if-then planning makes people highly sensitive to the cues that they have written down, and means that they can act swiftly and effortlessly as soon as these cues are encountered, thus environmentally cued habits are established. Implementation intentions remove the burden of having to think about and remember when to act by using environmental cues to trigger the desired behaviour. The load on prospective memory is reduced as habitual responses are established (e.g. first cup of tea at breakfast in the kitchen cues taking morning medication). In a recent example, Brown et al. [17] showed that a simple if-then plan in epilepsy patients resulted in intervention participants showing improved adherence relative to controls on all three outcomes: doses taken in total (93.4% vs. 79.1%), days that correct dose was taken (88.7% vs. 65.3%), and doses taken on schedule (78.8% vs. 55.3%), all p < .01. Importantly, participants with the greatest degree of cognitive impairment benefited most from the intervention [17].

### Framework

We have developed our intervention using the new Medical Research Council (MRC) Guidance on developing and evaluating complex interventions [18]. We have completed the development work of the MRC framework and have identified the evidence base, utilised an appropriate theoretical model of adherence (self-regulation), and identified process variables that relate to both intentional and non-intentional adherence. We now wish to embark on feasibility/piloting where we will test a brief intervention, in terms of recruitment, retention, acceptability and efficacy, and use the results of the pilot to inform the sample sizes required for a larger, more definitive trial. The intervention has two components, tackling both intentional and non-intentional non-adherence, and each component has a strong, supportive evidence base.

We recently found that 30% of stroke patients reported sub-optimal medication adherence at interview. Approximately one third of the variance in self-reported poor adherence was predicted by the following four variables: (1) younger age, (2) greater cognitive impairment, (3) lower perceptions of medication benefits, and particularly, (4) greater specific concerns about medications (toxicity, side effects etc.) [15]. Our qualitative interview findings confirmed the questionnaire results by showing that (a) medication concerns were key determinants of medication taking behaviour and also (b) the establishment of a habitual routine for medication taking was seen as vital. The findings from that study justify the evaluation of a pilot intervention trial aimed at targeting both intentional and non-intentional components, with the goal of improving medication adherence.

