## Methods/Design

### Recruitment

In order to maximise recruitment and the representativeness of the sample, we shall attempt to recruit and obtain consent from consecutive patients who are discharged from the Edinburgh Western General Hospital stroke units and clinics and who are prescribed secondary antihypertensive medication. Our previous experience suggests that this approach will significantly improve trial recruitment. Currently approximately 300 in-patients and 400 out-patients are discharged per year, with over 60% prescribed antihypertensive medication. We will screen 400 first-time stroke (ischaemic and haemorrhagic) or Transient Ischaemic Attack (TIA) patients, and expect a 75% response rate (300). We plan to include both stroke and TIA patients since both groups of patients are treated in a similar way with secondary prevention drugs and are likely to have similar issues with respect to non-adherence [9]. We have decided to focus on the early months following stroke in order to maximise the likelihood of preventing a further stroke. Poor adherence will have a much greater effect on stroke risk in the first few months because the risk of stroke (and thus the absolute risk reductions associated with drug treatment) is highest at this stage [19]. Furthermore, following Petrie et al. [20], we believe that the efficacy of the intervention will be enhanced by eliciting and correcting dysfunctional stroke and medication beliefs soon after preventative drugs are started. However, we have to strike a careful balance between early intervention, and also allowing enough time for participants to demonstrate variance in adherence, so that we can specifically target those showing sub-optimal adherence, thus our decision to assess adherence at 3 months post stroke or TIA. Consenting participants will therefore be contacted by post 3 months after their event and asked to complete the Medication Adherence Self Report Scale (MARS) [21] and return it in a stamped addressed envelope. In this mailing, we will also ask participants to complete the Brief Illness Perceptions Questionnaire [22] and the Beliefs about Medication Questionnaire [23]. This will allow us to economically test the robustness and replicability of the association we previously observed between specific medication concerns and self-reported adherence in a new large sample of TIA/stroke patients. We will then invite all those reporting sub-optimal adherence on the MARS (score of 24 or less) to participate. Based on our earlier study we conservatively estimate that approximately 30% will report some degree of poor adherence, and of those, up to 30% may then decline to participate. We therefore estimate that if we invite 90 patients, 60 will agree to participate. They will then be randomly allocated to brief intervention or treatment as usual (TAU). We are allowing for a further 10% attrition rate during the trial, however, one of the main purposes of this pilot is to obtain data on uptake, acceptability and attrition.

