### Design

A pilot RCT with patients allocated to intervention versus treatment as usual (TAU). Web-based randomisation at the patient level into intervention or TAU will be provided by the Edinburgh Clinical Trials Unit, using minimisation with a random element to ensure that the two trial arms are not significantly different on three key variables: age, number of pills taken per day and baseline MARS adherence. A CONSORT flowchart of the trial design is shown in Figure 1.

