### Control variables

At Session 1, following Trewby et al. [29] and our previous study, all participants will be asked to complete a baseline measure of their perception of the benefit (0-100%) provided by their current stroke prevention medication using a simplified graphical presentation card. Participants will also complete the Mini-Mental State Examination (MMSE), as we previously demonstrated that younger age, lower MMSE and low perceived benefit of medication were all related to poor adherence [15]. Finally, we will determine whether these, and other baseline characteristics (e.g. prior use of reminder packaging and partner involvement in reminding to take medication), are related to treatment outcome.

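### Baseline medication concerns, singled out as a predictor and in hand before allocation, are not named as a control variable or model covariate: a missed gain in precision, not a bias

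*Protocol article*

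**What the plan says.** The Framework section reports the earlier study in stroke patients: "Approximately one third of the variance in self-reported poor adherence was predicted by the following four variables". The four are younger age, greater cognitive impairment, lower perceived benefit, "and particularly, (4) greater specific concerns about medications (toxicity, side effects etc". The interviews in the same study pointed the same way: "medication concerns were key determinants of medication taking behaviour". The section on intentional non-adherence also treats concerns as a main driver.

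Under Recruitment, the mailing three months after the event carries the MARS, and in it "we will also ask participants to complete the Brief Illness Perceptions Questionnaire [22] and the Beliefs about Medication Questionnaire [23". Patients scoring 24 or less on the MARS are invited, and of those who agree the article says "They will then be randomly allocated to brief intervention or treatment as usual (TAU". The concerns score is therefore available before allocation.

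The Design section minimises on "three key variables: age, number of pills taken per day and baseline MARS adherence". The Control variables section justifies its Session 1 measures from the earlier study: "we previously demonstrated that younger age, lower MMSE and low perceived benefit of medication were all related to poor adherence". It then promises to see whether these and other baseline characteristics relate to outcome. The Analysis section describes a two-group, three-time-point repeated-measures analysis and names no covariate.

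**The concern.** The same earlier study is cited twice. In the Framework section it yields four predictors with the fourth stressed. In the Control variables section it yields three, and the stressed one is missing without explanation. The missing one is already in hand from the mailing, whereas perceived benefit has to be collected at Session 1.

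What is at stake is the precision of the effect estimate. Research question (d) and the Analysis section make the observed effect size, with its 95% confidence interval, a main product of the pilot. The Intervention section has the MEMS bottles first filled at the end of Session 2, so all three monthly readings follow both intervention sessions and there is no MEMS baseline to adjust for. Prior differences between patients can be taken out only through questionnaire and other baseline measures. An effect already present in the first month shows as a difference between arms, not as an interaction with time, and that difference is where a prognostic covariate helps.

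**Working it through.** The plan gives no figure for what adjustment would gain. The only related one is the share of about one third of the variance in *self-reported* adherence, for four predictors jointly. The power statement in the Analysis section is a separate matter and is not used here.

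**Inputs**
- 30 patients per arm, 60 in all (Analysis).
- r, the correlation of baseline concerns with MEMS adherence: not in the document. Assumed 0.30 to 0.40, that is 9% to 16% of variance. For scale, one quarter of one third is 1/12 = 8.3% (r = 0.29). The whole third (r = 0.58) is an upper bound that gives concerns all the credit.

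**1. Chance imbalance.** Without balancing on concerns, the standardised baseline difference between arms has standard deviation √(2/30) = 0.258.

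**2. Effect on the unadjusted arm difference.** The shift has standard deviation r × 0.258: 0.077 SD at r = 0.30 and 0.103 SD at r = 0.40. The 95% range is 1.96 times that, ±0.15 to ±0.20 SD. The ordinary standard error already includes this variation.

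**3. Is it a bias?** In 20,000 simulated null trials of 30 per arm for each case, with concerns explaining 10%, 20% or 33% of variance, the unadjusted test rejected in 4.9% to 5.1%. In the roughly 5% of trials with an imbalance above 0.5 SD it rejected in 12% to 23%, but this is offset over the remaining trials.

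**4. Gain from adjustment.** The standard error is multiplied by √(1 − r²). The equivalent number of extra patients is 60/(1 − r²) − 60.

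| Variance share r² | r | SE factor | Interval narrower by | Extra patients |
|---|---|---|---|---|
| 0.05 | 0.22 | 0.975 | 2.5% | 3.2 |
| 0.09 | 0.30 | 0.954 | 4.6% | 5.9 |
| 0.16 | 0.40 | 0.917 | 8.3% | 11.4 |
| 0.33 (upper bound) | 0.58 | 0.816 | 18.4% | 30.0 |

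These factors treat the slope as known. Estimating it multiplies the variance by about 1 + 1/(60 − 4) = 1.018. The two middle SE factors become √(0.91 × 1.018) = 0.962 and √(0.84 × 1.018) = 0.925, which takes back a little under one percentage point.

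**5. The interaction.** If concerns act with slope b in every month and the arms differ by d at baseline, the arm difference moves by b × d in each month and cancels from any comparison between months. If the slope changes from b1 to b3, the change over time moves by (b3 − b1) × d. The covariate therefore bears on the interaction only if concerns predict change.

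**The case against.** **Unnamed is not excluded.** A reader might infer that concerns were rejected as a control variable. The document does not say so. The restated predictors explain why extra measures are taken at Session 1, the Timetable counts the BMQ as baseline data, and the closing reference to other baseline characteristics is open-ended. This stands. But that clause promises only to look at relations with outcome, not to adjust the arm comparison.

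**The covariate list may sit in an analysis plan that is not shown.** This is fair for model detail. The point here is narrower: the article itself selects predictors from its earlier study and leaves out the one it stressed.

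**Mimicking or masking an effect.** A reader might infer that chance imbalance on concerns threatens the validity of the result. It does not: the simulated overall type I error is unchanged. Setting the ±0.15 to ±0.20 SD shift against the 0.2 in the Analysis section is not like for like either, since that figure is tied to the interaction, from which a stable shift cancels.

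**The BMQ is well used already.** It tailors Session 2, serves a replication of the concerns–adherence association under Recruitment, and enters the mediation test. None of these uses adjusts the comparison of arms.

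**The correlation is assumed and probably too high.** The one third refers to self-report, not MEMS. Restricting entry to MARS 24 or less, and minimising on MARS and age, should weaken the residual association or the imbalance. This stands, although Measuring Adherence concedes ceiling effects in the MARS.

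**Minimisation.** A reader might infer that concerns ought to be a minimisation factor. With 60 patients, the choice to balance on baseline adherence, age and pill count is a reasonable design judgement, and nothing in the document shows it to be wrong.

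**Conclusion.** The inconsistency between the Framework and Control variables sections is real, and it leaves a small, nearly free gain in precision untaken. For the between-arm difference the gain is an interval about 5% to 8% narrower, or about 6 to 11 patients on 60. This assumes a correlation of 0.30 to 0.40 with MEMS adherence, and it would be smaller if selection and balancing on the MARS weaken that correlation. For the interaction there is a gain only if concerns predict the course of adherence over the three months. Neither the validity of the randomised comparison nor the choice of minimisation factors is in question.

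**What to change.** - In the Control variables section, name the BMQ specific-concerns score from the postal mailing.
- In the Analysis section, enter it as a prespecified continuous covariate, with its interaction with time, in the MEMS model. Report the adjusted arm difference over the three months with its confidence interval, alongside the interaction.
- When Session 3 concerns are compared between arms, use the same postal score as the covariate.

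The cost is a sentence or two of text and three parameters: one of the 60 − 2 = 58 between-patient degrees of freedom and two of the 58 × 2 = 116 within-patient ones. It needs no new data, visits or patients, and no change to the allocation.
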